### Primary outcome measures

***The Rosenberg self-esteem scale*** (Rosenberg, 1965) was used to assess feelings of self-worth. This scale consists of ten items, each item is rated on a 4-point scale where 4 = “strongly agree”, 3 = “agree”, 2 = “disagree” and 1 = “strongly disagree”. An example of an item includes “I take a positive attitude towards myself”. Some items are negatively worded for instance “I certainly feel useless at times” and these have been reversed scored in final scoring process. Items were added up with possible scores for the scale ranged from 10 to 40 were higher scores are indicative of greater self-esteem. The Rosenberg self-esteem scale has been widely used and has been reported to have great internal consistency (Chronbach’s α = .88) and validity scores (Rosenberg, 1965; Rosenberg and Simmons, 1971; Simmons et al., 1973).

The ***eating disorders assessment*** [Clinical Interview Assessment, (CIA)] developed by Bohn and colleagues (Bohn et al., 2008) (16-items scale) was used to assess psycho-social impairment induced by eating disorders. Participants were asked to indicate over the past month, to what extent have their eating habits, exercising, or feelings about your eating, shape or weigh caused them impairment in three areas including cognitive “made you feel upset”, personal “Interfered with you doing things you used to enjoy” and social “made it difficult to eat out with others”. Each item is scored on a 4-point response format 0 = “not at all”, 1 = “slightly”, 2 = “moderately” and 3 = “a lot”. The scale scores ranged from 0 to 48, higher scores are indicative of greater impairment and eating disorders. This scale has demonstrated high internal consistency and test-retest reliability and good validity (Bohn et al., 2008).

### Secondary outcome measures

***Body satisfaction*** was measured by the body esteem scale developed by Katz-Mendelson and White (1982) which was found to be a reliable instrument with children as young as 7 years old. The 24 items in this scale encompass how a person values their appearance and body. There are equal numbers of positive and negative items and participants are asked to agree or disagree with each item. An example of a positive item is “I’m proud of my body” and a negative item is “I wish I was thinner”. The scale is scored by counting the number of responses indicating positive body esteem (maximum score is 24). A high score on the scale reflects higher body satisfaction.

***Body Dissatisfaction*** was measured with a subscale of the Eating Disorders Inventory (Garner et al., 1983). The scale contained 9 items designed to measure dissatisfaction with specific body parts. Examples of items include “I think my hips are too big” and “I think that my stomach is just the right size”. Responses were rated on a 6 point scale where 1 = never and 6 = always. Scores ranged from 0 to 54, with higher scores indicating higher dissatisfaction.

***Self-efficacy*** was measured by a self-efficacy scale designed to assess individuals’ sense of competence in particular areas. We used Froman and Owen’s (1991) health self-efficacy measure designed for use with high school students. The 43 item scale has two subscales, *physical health self-efficacy* and *mental health self-efficacy*. Participants are asked to indicate their degree of confidence where 1 = “a little” and 5 = “a lot” in their ability to complete a number of tasks. An example of task from *physical health self-efficacy scale* include “treating a fever” and *mental health self-efficacy scale* “maintaining a positive attitude towards school”. This scale was slightly refined to suit the current study’s participants. For example some items such as “avoiding illegal drugs”, were removed to make the scale appropriate for younger age participants. The final scale used had 37 items, scores for the scale ranged from 37 to 185 were higher scores are indicative of greater *physical health* or *mental health self-efficacy*.

***Dieting behavior*** was assessed by the Dutch Eating Behaviour Questionnaire for Children (van Strien and Oosterveld, 2008) comprised of three subscales including: *restrained eating*, *emotional eating* and *external eating*. The scale is designed to assess the degree of concern a participant has about dieting and restricting the amount of food they may otherwise eat. There are a total of 20 items. Participants are asked to circle either yes, no or sometimes to a statements such as *restrained eating subscale*: “If you have eaten too much do you eat less than usual the next day?”; *emotional eating subscale*, “if you feel depressed do you get a desire for food?” and *external eating subscale* “do you feel like eating whenever you see or smell food?”. Each item is scored on a 3-point response format no (0), sometimes (1), yes (2). The scores are then summed up and higher scores represent higher dieting behaviour. Scores range from 0–48. This scale has demonstrated excellent reliability, Cronbach’s α = 0.80 *restrained eating*, Cronbach’s α = 0.81 *emotional eating*, and Cronbach’s α = 0.74 *external eating*, (van Strien et al., 1986; van Strien and Oosterveld, 2008) and has been widely used (Higgins and Gray, 1998; Carter et al., 1997; Higgins and Altman, 2008).

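### The dieting behaviour score adds emotional and external eating to restrained eating, so a change in dieting can be diluted or masked; two secondary score ranges also contradict their own items

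*Protocol article*

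**What the plan says.** All the score definitions at issue are in the protocol article under Secondary outcome measures.

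**Dieting behaviour.** The questionnaire is said to have three subscales (restrained, emotional and external eating), with a reliability coefficient for each. Its purpose is stated as: "The scale is designed to assess the degree of concern a participant has about dieting and restricting the amount of food they may otherwise eat". On size and scoring the article says "There are a total of 20 items", codes each item 0, 1 or 2, and continues "The scores are then summed up and higher scores represent higher dieting behaviour". One range follows: "Scores range from 0–48".

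**Body dissatisfaction.** There are nine items, each rated from 1 to 6. The article then says "Scores ranged from 0 to 54, with higher scores indicating higher dissatisfaction".

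**Self-efficacy.** The instrument has a physical health and a mental health subscale, with items rated from 1 to 5. After some items were removed, "The final scale used had 37 items, scores for the scale ranged from 37 to 185". The same sentence reads higher scores as greater physical health or mental health self-efficacy.

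The hypothesis, at the end of the Background, lists dieting behaviour once and the two kinds of self-efficacy separately. The Analyses section makes raw summed scores the dependent variables of the mixed models.

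**The concern.** The dieting hypothesis is to be tested on a score whose label does not match its content. If the rule is followed as written, a girl who restricts less but eats more when upset may show little or no change. A girl whose emotional eating improves, with no change in restriction, is recorded as dieting less. A null result on the total could hide a real fall in restraint, and a favourable result could come from something other than dieting.

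The ranges are a smaller matter. Where a stated range cannot arise from the stated items and coding, one of the three is wrong, and the article does not show which. A reader cannot then reproduce the score.

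**Working it through.** **1. Ranges.** The possible range of a summed scale runs from items × lowest item score to items × highest item score. Inputs are from Primary outcome measures and Secondary outcome measures.

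| Scale | Items | Item score | Computed | Stated |
|---|---|---|---|---|
| Self-esteem (primary) | 10 | 1–4 | 10–40 | 10–40 |
| Impairment (primary) | 16 | 0–3 | 0–48 | 0–48 |
| Body esteem | 24 | 0–1 | 0–24 | maximum 24 |
| Self-efficacy, all items | 37 | 1–5 | 37–185 | 37–185 |
| Body dissatisfaction | 9 | 1–6 | **9–54** | 0–54 |
| Dieting behaviour | 20 | 0–2 | **0–40** | 0–48 |

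Four of the six reproduce and two do not. Other codings do not rescue the two failures:

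- Dieting: a maximum of 48 with items scored 0–2 needs 48/2 = 24 items, not 20. Coding the 20 items 1–3 gives 20–60.
- Body dissatisfaction: coding the nine items 0–5 gives 0–45.

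**2. Self-efficacy.** The stated range is exact for the whole scale. A subscale of k items runs from k to 5k with k below 37, so neither subscale can have the range 37–185. The article does not give k.

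**3. Content of the dieting total.** The sample items, set beside the stated purpose (concern about dieting and restricting food):

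- Restrained: eating less the day after eating too much. This is restriction.
- Emotional: wanting food when depressed. This is not restriction.
- External: feeling like eating on seeing or smelling food. This is not restriction.

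Reliability is given for each subscale (0.80, 0.81 and 0.74) and not for the total.

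**4. Size of the dilution (illustration).** The article gives no subscale variances or correlations. Assume three subscales of equal variance, set to 1, with common correlation r. The variance of the total is 3 + 6r. If only restraint changes, by 0.5 SD, the change on the total in SD units is 0.5/√(3 + 6r):

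- r = 0: 0.5/√3 = 0.29
- r = 0.3: 0.5/√4.8 = 0.23
- r = 0.5: 0.5/√6 = 0.20

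If another subscale moves by 0.5 SD in the opposite direction, the numerator is 0.5 − 0.5 = 0 and the total does not move. If emotional eating alone falls by 0.5 SD, the same formula shows a fall of 0.20 to 0.29 SD, which would be read as less dieting.

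**The case against.** The summing sentence does not say that it runs across subscales, and the per-subscale reliabilities fit an intention to score them separately. An analysis plan that is not shown could specify that. This is fair as far as it goes. But the article states one rule, one direction of interpretation, one range and one hypothesised outcome, so a single total is the natural reading, and this is a stated rule rather than an omitted detail.

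Three stronger readings are tempting, and the documents do not support them:

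- *A reader might infer that the dieting hypothesis cannot be answered at all.* The illustration shows dilution, with 0.20 to 0.29 SD of a 0.5 SD change remaining. Full cancellation needs an equal and opposite change elsewhere, and nothing in the article says the program would produce one; the program description speaks of promoting healthy eating and reducing dieting.
- *A reader might count the self-efficacy range as a third impossible one.* It is correct for the 37-item total, and the hypothesis already lists the two subscales separately. What remains is loose wording.
- *A reader might infer from the two ranges that the data were scored differently from the description.* The printed ranges may simply be misprints. A range is not an input to the mixed model or to the power analysis, which rests on self-esteem. If body dissatisfaction items were in fact coded 0–5 and not 1–6, every complete score would shift by 9 points and the treatment estimate would be unchanged.

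The equal-variance assumption is also open to question, since 20 items do not divide equally into three subscales. The figures show the order of the dilution, not an estimate for this trial.

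**Conclusion.** The point holds for the dieting score. As written, the rule produces a total that does not isolate what the dieting hypothesis is about, and a change in restraint would be weakened on it to roughly 40% to 58% of its size (0.20/0.5 to 0.29/0.5) under equal variances and correlations from 0 to 0.5. That conclusion rests on reading the rule as one total and on the sample items representing their subscales.

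Two stated ranges, and only two, contradict the items described: the dieting maximum is 8 points too high (48 against 40) and the body dissatisfaction minimum is 9 points too low (0 against 9). These are errors of description unless a check of the scoring shows otherwise. The self-efficacy passage needs clarification only. No primary outcome is touched. The change is worth making before analysis because it is cheap and bears on a named hypothesis.

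**What to change.** - Score and analyse restrained, emotional and external eating separately, and name restrained eating as the outcome for the dieting hypothesis. Keep the total, if at all, as a descriptive score that is not labelled dieting.
- Check the item counts and coding of the dieting and body dissatisfaction scales against the questionnaires and the scoring code, and correct whichever is wrong. If the items and coding stand as described, the ranges become 0–40 and 9–54.
- State that physical and mental health self-efficacy are scored as two subscales, with the item count and range of each, and present 37–185 as the range of the whole scale.

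**Cost.** The article describes data collection in the past tense and analysis in the future tense, and the scales are scored by item, so no new data should be needed: only scoring syntax and wording. Three eating scores in place of one add 3 − 1 = 2 secondary tests in each of the two studies. Naming restrained eating in advance as the one that answers the dieting hypothesis limits the effect of those extra tests on interpretation.

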### Procedure

#### Ethics and trial registration

The randomised control trial was prospectively registered with the Australian and New Zealand Control Trial Registry (ACTR 12610000513011). The trial was conducted in two phases that comprised Study 1 and Study 2.

Study 1 was prospectively registered with the Australian and New Zealand Control Trial Registry (ACTRN12610000513011). We then received notification of further funding to conduct this and Study 2. We submitted an amendment to our ethics application (ethics approval 10119B) to conduct Study 2 with the Monash Health Human Research Ethics Committee as the population of Study 2 and study design only varied slightly from Study 1 (Study 1 involved high school students and had a stepped wedge design of 3 schools being provided with the intervention per term, while Study 2 involved primary school students and had a stepped wedge design of 2 schools being provided with the intervention per term). We then amended the Australian and New Zealand Control Trial Registry so that the sample size listed on the registry was increased from 60 to 120 participants.

#### Study 1

High schools that contacted the Greater Dandenong Community Health Service in 2010 to receive the “Girls on the Go!” program that year were notified of the research and that their school’s placement on the waiting list that year would be determined at random. School welfare officers and teachers forwarded to the Greater Dandenong Community Health Service the list of student names who they determined met the study and program inclusion criteria. An investigator (LT) gained consent from participant’s parents (with assent from the participant) to participate in the research from all referred students. This investigator administered the data collection surveys at baseline and follow-up assessments at the time points indicated (Figures 1 and 2). The program was provided to schools in the order determined by the matched, random allocation sequence.

#### Study 2

The same recruitment and data collection approaches were used for study 2, though with recruitment derived from primary schools, and the addition of one further follow-up assessment.

### Analyses

The effect of being exposed to the “Girls on the Go!” program will be examined using a linear mixed model analysis approach, suitable for analysing longitudinal data where there is likelihood of missing data or loss to follow-up. The model that will be constructed to conduct this analysis will require construction of an independent variable, labelled “Girls on the Go”. This variable will be coded a 0 for observations where the group had not yet been exposed to the “Girls on the Go!” intervention (e.g. In study 1; at baseline for all schools and also at the first follow-up assessment but only for schools in the “Waiting List” period–see Figure 1), and 1 for observations where the participants had already received the “Girls on the Go!” intervention (e.g. In study 1; at the first follow-up assessment for schools in the first “Girls on the Go” period and also for all schools at the second follow-up assessment). Raw summative outcome measurement scores will be used as the dependent variables.

The mixed model analysis will involve investigating the effect of the “Girls on the Go” variable on the dependent variable, adjusting for assessment number (to account for the effect of time). The “Girls on the Go” variable will be entered into the model as a fixed factor, while assessment, student and school will be entered as random factors. Assessment will be nested within student which will be nested within school which will create a 3-level model that takes into account the longitudinal, clustered nature of data collected in this study. Maximum likelihood methods of estimation will be employed to address issues of missing data under the assumption of Missing At Random.

To investigate whether the effect of the “Girls on the Go!” program was sustained, a “Girls on the Go” by assessment interaction effect will be added to the same analysis models. A significant interaction effect in these models will indicate whether any changes brought about at the initial post-“Girls on the Go!” follow-up assessment were sustained. We will also examine the data from the group that received the “Girls on the Go!” program first and compare student results between the first and subsequent post-intervention follow-up assessments in isolation using linear regression clustering data by individual student.

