### Design

This study comprised a stepped wedge, cluster randomised controlled trial that was conducted in two phases on the basis of student population (Study 1 = secondary school age participants; Study 2 = primary school age participants). Stepped wedge designs are similar to cross-over trials, however only involve uni-directional cross-over resulting in all participants receiving the intervention by the conclusion of the trial. The waiting list for the “Girls on the Go!” program was used to generate the control period. The intervention program was designed to be delivered to a group of participants from the same school at the same time, thus randomising students in clusters (school) was seen as an appropriate unit of randomisation.

A total of 12 schools that requested the program were separated into Study 1 or 2. Within each study, schools were matched on the basis of number of students (into triplets for Study 1 and pairs for Study 2) and then randomly allocated (computer generated sequence developed by investigator blinded to school identity) to receiving the intervention immediately or having a waiting list period. Study 1 had one waiting list period of one school term, creating two steps in the stepped-wedge design (i.e. 3 schools were provided with “Girls on the Go!” each term over 2 terms–see Figure 1). Study 2 had two waiting list periods of one and two school terms, creating three steps in the stepped-wedge design (i.e. 2 schools were provided with “Girls on the Go!” each term over 3 terms–see Figure 2).

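### The Analyses section promises adjustment for time, but the model it specifies enters assessment only as a random term nested within student and so does not deliver that adjustment

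*Protocol article*

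**What the plan says.** All the relevant wording is in the Analyses section of the protocol article.

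- **Intent.** The effect of the programme variable is to be examined "adjusting for assessment number (to account for the effect of time").
- **Fixed part.** The programme variable "variable will be entered into the model as a fixed factor". No other term is given fixed status.
- **Random part.** The same sentence continues "while assessment, student and school will be entered as random factors".
- **Structure.** "Assessment will be nested within student which will be nested within school which will create a 3-level model".
- **Exposure coding, Study 1.** The variable is 0 "at baseline for all schools and also at the first follow-up assessment but only for schools in the" waiting-list period. It is 1 at the first follow-up for schools already served and "also for all schools at the second follow-up assessment".
- **Sustainability.** A programme-by-assessment interaction is added later, to ask whether any effect lasts.

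The Design section supplies the steps: "Study 1 had one waiting list period of one school term, creating two steps in the stepped-wedge design", with three schools per step. Study 2 has three steps of two schools. The Study 2 paragraph under Procedure adds one follow-up assessment, so there are three assessments in Study 1 and four in Study 2.

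**The concern.** The stated intent and the stated model do not match. An assessment effect nested within student has mean zero and is independent from one student to the next. Each student has one record per assessment, so this term is simply the residual. It cannot carry a shift that all students share at a given assessment, and that shift is what adjustment for time has to remove.

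This matters more in a stepped wedge than in a parallel trial, because exposure rises with time by design. If the model has no common time effect, part of any general change over the terms is read as programme effect. Such change is plausible here: the Inclusion criteria select girls partly for low self-esteem or poor body image, and they complete the same questionnaires repeatedly. Regression to the mean, retest effects and maturation could all move scores. The pilot section itself gives the limits of pre-post comparison as the reason for a randomised trial, and a model without a common time effect brings part of that limitation back. The model governs both primary outcomes in both studies.

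**Working it through.** The documents give no figure for bias or error rate under this model, so there is none to reproduce. The check asks what the specified model estimates when the programme does nothing.

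**Inputs from the documents.** Exposure sequences: Study 1, 0-1-1 (three schools) and 0-0-1 (three schools); Study 2, 0-1-1-1, 0-0-1-1 and 0-0-0-1 (two schools each). Cluster size 10 and ICC 0.33 (Power analysis).

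**Assumptions.** ICC from 0.05 to 0.33. Within-student correlation from 0.3 to 0.6 of the variance left after the school component. Total SD 1, two-sided alpha 0.05, no school-by-term noise. The drift is also assumed, since the documents give none.

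**Step 1: bias by hand.** With random school and student intercepts and no fixed time, the estimate is driven mainly by within-student change. Let x be exposure centred within its sequence. A common time pattern g(t) then gives an expected programme coefficient of Σx·g(t) / Σx², summed over the six schools.

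| | Σx² | Σx·t | Drift d per assessment | Σx·(t>0) | One-off shift r after baseline |
|---|---|---|---|---|---|
| Study 1 | 4 | 6 | 6/4 = 1.5d | 3 | 3/4 = 0.75r |
| Study 2 | 5 | 10 | 10/5 = 2.0d | 3 | 3/5 = 0.60r |

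Exact generalised least squares on 6 schools × 10 students, which also uses a little between-student information, gives 1.46d–1.50d and 1.93d–1.99d for drift, and 0.73r–0.75r and 0.58r–0.60r for the shift, over the assumed ranges.

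**Step 2: standard error.** Approximately √(σ²e / (10·Σx²)), where σ²e is the residual variance. At ICC 0.33 and correlation 0.6, σ²e = 0.67 × 0.4 = 0.268.

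- Study 1: √(0.268/40) = 0.082 SD.
- Study 2: √(0.268/50) = 0.073 SD.

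**Step 3: false positives at an assumed drift of 0.1 SD per assessment.** The rate is P(|Z + bias/SE| > 1.96), from the exact values.

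| | ICC 0.05, correlation 0.3 | ICC 0.33, correlation 0.6 |
|---|---|---|
| Study 1 | bias 0.146, SE 0.127: 21% | bias 0.150, SE 0.082: 45% |
| Study 2 | bias 0.193, SE 0.113: 40% | bias 0.199, SE 0.073: 78% |

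A simulation of 2,000 runs in the right-hand case gave 44.9% and 76.8%.

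**Step 4: assessment as a categorical fixed effect.** The expected coefficient is exactly 0 in both studies for any time pattern common to all students, and nominal size is 5% (simulated 5.6% and 5.3%). Once assessment means are also removed from exposure, Σx² falls from 4 to 1 in Study 1 and from 5 to 1.667 in Study 2. The standard errors become √(0.268/10) = 0.16 and √(0.268/16.67) = 0.13 SD.

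**Step 5: other meanings of a random assessment term.** These were run at ICC 0.05–0.33 and total within-student correlation 0.5–0.7.

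- A student-level random slope with no fixed slope leaves 0.80d–1.48d (Study 1) and 0.53d–1.92d (Study 2), for slope variances 0.01 to 0.5.
- A random time factor crossed with students and schools leaves only about 0.06d–0.09d at a time variance of 0.5, but about 1.0d–1.4d at 0.01.

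**The case against.** The strongest reply is that the section openly commits to adjusting for assessment number. On that view the nesting sentence only describes the levels of the data, with assessment as the level-1 unit. The programme-by-assessment interaction would normally presuppose an assessment term among the regressors, and the text never says the programme variable is the *only* fixed factor.

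Part of this stands. The intent to adjust is explicit, so a reader who infers that the plan makes no provision for time goes too far; the fault is a contradiction between intent and specification. The rest does not rescue the model. The sentence contrasts the fixed programme variable with assessment as a random factor, so an analyst who follows it fits the biased model. The interaction is added only for the sustainability question, and no fixed main effect of assessment is stated for the primary model. A crossed random time factor would reduce the bias when its variance is large, but the stated nesting rules that reading out.

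Two further inferences are tempting and unsupported. One is that all regression to the mean is credited to the programme, so that the randomised waiting list is worth nothing: a one-off shift after baseline is credited in part, at 0.75r and 0.60r. The other is to quote 45% and 78% as the error rates: they are the upper end of a range, at a total within-student correlation of 0.33 + 0.67 × 0.6 = 0.73, under a drift that the documents do not give.

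**Conclusion.** The point holds as an internal contradiction that needs correcting: the Analyses section announces a time adjustment that its own model does not make. That conclusion rests on the text and the design alone. The bias multipliers of about 1.5d and 2.0d for drift, and 0.75r and 0.60r for a single shift, follow from the exposure sequences and vary little with the correlations.

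The false-positive ranges of 21–45% and 40–78% rest on the assumed 0.1 SD drift, the assumed correlations and a normal approximation with known variances. With six schools per study the true rates would differ somewhat. If scores show no common trend, the model as written has no bias of this kind.

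**What to change.** Replace the sentence on fixed and random factors with: *The programme indicator and assessment number (categorical: 3 levels in Study 1, 4 in Study 2) are fixed effects; school and student within school are random intercepts.* Delete assessment from the list of random factors. If a fixed assessment effect was always intended, the same edit makes that plain.

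The cost is one sentence and a larger standard error: about 0.16 against 0.08 SD in Study 1, and 0.13 against 0.07 SD in Study 2, at ICC 0.33 and correlation 0.6. The smaller figures are valid only if there is no common time trend.

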### Power analysis

Analysis of data from the pilot study indicated that the effect of the “Girls on the Go!” program on participant self-esteem was very strong (ie. Change in outcome is 1.5 times the width of the standard deviation). Assuming 80% power, only 10 participants per group will be required in a standard randomised trial with randomisation of individual participants. This study will be a cluster randomised trial however to account for a variance inflation factor (design effect) of 3 (where average size per cluster is n =10, and the ICC is assumed to equal 0.33) then a total of 120 participants in both the primary (n = 60) and secondary (n = 60) schools will be required.

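### The three-level model has no school-by-assessment term, so the programme effect's standard error is too small if schools drift differently between assessments

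*Protocol article*

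**What the plan says.** Under Design, the protocol article states "A total of 12 schools that requested the program were separated into Study 1 or 2". For Study 1, "Study 1 had one waiting list period of one school term, creating two steps in the stepped-wedge design", with three schools starting per term; for Study 2, "Study 2 had two waiting list periods of one and two school terms, creating three steps in the stepped-wedge design", with two schools starting per term. Each study therefore has six schools.

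Under Analyses, the programme indicator is a fixed factor, and assessment, student and school are listed as random factors. Assessment is nested in student and student in school, "which will create a 3-level model that takes into account the longitudinal, clustered nature of data collected in this study". On estimation, the section says "Maximum likelihood methods of estimation will be employed to address issues of missing data", on a Missing At Random assumption. It describes no component shared by the girls of one school at one assessment. It names neither a test statistic nor a degrees-of-freedom method.

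The only correlation given is in the Power analysis: "where average size per cluster is n =10, and the ICC is assumed to equal 0.33".

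**The concern.** In the stated structure, the assessment-level deviation sits below the student, so it is independent between girls of the same school. The school effect is a single intercept. Together these assume that a school stands at the same distance from the average at every assessment. Any shared movement of a school group between terms has no place in the model and is absorbed into student-level residual noise.

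The protocol gives reasons to expect some shared movement. Each group comes from one school and attends together, the programme description says that strong bonds form within the group, and content and duration may be adapted to the group.

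The programme effect is estimated mainly from change within schools. If that change has a school-level component, the relevant replication is the small number of school-by-assessment cells, whereas the model uses the much larger number of student observations. Confidence intervals for both primary outcomes, in both studies, would then be too narrow, and an ineffective programme could appear significant too often.

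**Working it through.** **The plan's own figures.** The protocol states no type I error or standard error for this model. Its sample size reproduces from the stated design effect: 2 groups × 10 × 3 = 60 per study. The design effect does not follow from its stated inputs, because 1 + (10 − 1) × 0.33 = 3.97, and a value of 3 needs an ICC of 2/9 = 0.22. That is a separate matter, but it shows that 0.33 is only a planning value, so a lower ICC is also tried.

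**Inputs from the documents.** Six schools per study; 10 girls per school; ICC 0.33; three assessments in Study 1 (baseline, first follow-up, and programme coded 1 "also for all schools at the second follow-up assessment"); four in Study 2 ("the addition of one further follow-up assessment", Procedure, Study 2).

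**Assumptions.** Total variance 1; complete data; assessment as a fixed categorical effect; 60% of within-school variance stable per student; a share *s* of the school variance that is school-by-assessment, with *s* = 0, 5%, 10% or 20%; Wald z at 1.96.

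**Hand check, Study 1, ICC 0.33, *s* = 10%.**
- Student residual variance: 0.67 × 0.4 = 0.268.
- School-by-assessment variance: 0.10 × 0.33 = 0.033.
- True time-varying variance of a cell mean: 0.268/10 + 0.033 = 0.0598.
- Within-student residual df: 60 × 2 − 2 − 1 = 117. Of these, 5 × 2 − 1 = 9 carry the school-by-assessment variance, multiplied by 10.
- Residual variance seen by the stated model: 0.268 + 9 × 0.33/117 = 0.2934, or 0.0293 per cell mean.
- Reported over true standard error: √(0.0293/0.0598) = 0.70.
- Type I error: P(|Z| > 1.96 × 0.70) = 17%.

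The same steps give ratios of 0.81 and 0.59, and type I errors of 11% and 25%, for *s* = 5% and 20%.

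**Simulation of the stated model under no effect** (4000 runs per cell, Study 1 / Study 2):

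| Share *s* | SE ratio, ICC 0.33 | Type I, ICC 0.33 | Type I, ICC 0.10 |
|---|---|---|---|
| 0 | 1.00 / 0.97 | 5.2% / 5.9% | 5.4% / 6.2% |
| 5% | 0.80 / 0.79 | 11.4% / 12.2% | 6.7% / 7.8% |
| 10% | 0.70 / 0.69 | 17.2% / 17.7% | 8.3% / 9.3% |
| 20% | 0.58 / 0.58 | 26.0% / 25.3% | 11.0% / 11.6% |

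**Sensitivity to student stability.** In Study 1 at ICC 0.33 and *s* = 10%, changing the stable student share from 0.3 to 0.8 moves type I error from 13.6% to 25.6%.

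**Which part of the specification is responsible.**
- Changing only maximum likelihood to REML in the stated model moves the error by less than one point (for example 17.2% to 16.7%).
- With the school-by-assessment term added but maximum likelihood and z kept, error is still 8.5% to 13.7% in Study 1 and 8.9% to 11.0% in Study 2, for *s* from 5% to 40%.
- With the term, REML and a t reference, at ICC 0.33 and *s* = 5%, 10%, 20%, error is 3.7%, 4.4%, 5.1% in Study 1 and 5.0%, 5.1%, 5.4% in Study 2. At *s* = 0 it is 1.9% and 2.8%.

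**Degrees of freedom for the t reference** (cells minus schools, assessments less one, and programme):
- Study 1: 18 − (6 + 2 + 1) = 9.
- Study 2: 24 − (6 + 3 + 1) = 14.

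**The case against.** A reader might infer that the planned analysis simply has a type I error well above 5%. The documents do not support that. They give no school-by-assessment variance and no between-period correlation, and without such variance the stated model performs close to nominally. The share *s* and the stable student share are assumptions. ICC 0.33 is a planning value, and at ICC 0.05 with *s* of 10% or less the error is only 6% to 7.5%.

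A reader might also blame maximum likelihood. In the stated model it is a minor cause, because the effect is estimated largely within schools against many residual degrees of freedom. The wording on estimation may not even exclude restricted maximum likelihood.

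The Wald z-test is likewise a choice made for this check, and a small-sample method is commonly left to an analysis plan. The point therefore does not rest on its absence. Nor would a cautious reference distribution alone be a cure: at ICC 0.33 and *s* = 20%, a t-test on 4 df in the stated model still rejects 10.8% / 11.3% of the time.

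Two further reservations stand. Assessment is both adjusted for and listed as random, so treating it as a fixed effect is one reading. Group dynamics and facilitators act mainly after exposure, whereas the simulation spreads the extra variance over all cells; the simulated pattern is a simplification.

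What the objection does not remove is that the variance structure is fixed in the text. It is not a detail left open, and it sets to zero a component that delivery to intact groups makes plausible.

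**Conclusion.** The point holds conditionally. The stated three-level structure assumes that schools do not drift differently between assessments. If they do, the standard error of the programme effect is too small: by about 20% to 42% at ICC 0.33 for a drift share of 5% to 20%, with type I error of about 12%, 17% and 26% at shares of 5%, 10% and 20%. With no drift it is about 5% to 6%. At ICC 0.10 it is about 7% to 12%.

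These sizes rest on fixed time effects, complete data, a 60% stable student share and a Wald z-test. The documents do not settle the drift share or the stable share, so the figures show a risk and do not estimate the trial's actual error rate. The missing term is the main cause. The estimation method becomes important once that term is present, because only about 9 (Study 1) or 14 (Study 2) degrees of freedom remain.

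**What to change.** Revise the model statement under Analyses along these lines: random intercepts for school, school-by-assessment and student; programme and assessment number as fixed effects, with assessment categorical; estimation by REML; tests and confidence intervals on Kenward-Roger or Satterthwaite degrees of freedom. REML is as valid as maximum likelihood under Missing At Random, so the stated missing-data rationale is kept. Both parts are needed: the extra term, and the small-sample inference that goes with it.

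As a check, report a regression of school-by-assessment means on school, assessment and programme, with t on 9 df in Study 1 and 14 df in Study 2. In a separate simulation of 2000 trials per scenario, this check rejected between 4.0% and 5.6% of the time.

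The change is to wording only and needs no new data. Its price is wider intervals, some loss of power (not quantified here), and a conservative test, about 2% to 3% at the nominal 5%, if schools do not drift.
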